#### Covariates and subgroups

Covariates for adjustment in all analyses will include the randomisation stratification variable, gender, comorbidities, and age. Baseline adjustment will be performed for the primary outcome and all relevant secondary outcomes.

#### Multiple testing

The analyses will perform multiple tests on the unadjusted and adjusted, and possibly sensitivity analyses of the primary outcome. No adjustment for multiple comparisons of secondary outcomes is planned since these are considered less critical than the primary outcome.

#### Detailed analyses approach

For all analyses, differences between treatment groups will be reported with 95% confidence intervals, and statistical significance will be assessed at the two-sided 0.05 level.
Analysis of PIMs (primary outcome) between groups at 6 months will be performed using Poisson regression with adjustment of baseline values, age, comorbidities, and dialysis group. Secondary outcomes will be analyzed similarly, using either ordinary least squares or Poisson regression, as appropriate.Outcomes with repeated measures at 3 and 6 months, including the primary outcome, will be analyzed using mixed-effects models to account for correlated measurements within individuals over time. To assess differences between the two treatment groups, general linear models will include fixed effects for the treatment group, time point, and the interaction between the treatment group and the time point. Treatment effects will be reported separately at 6 months post-randomisation, regardless of the significance of the interaction term.For continuous outcomes, linear regression adjusted for baseline will be used without data transformations. Estimates of the treatment effect will be reported as mean differences in the change from baseline to 6 months between the intervention and control groups. For ordinal categorical outcomes, treatment effect estimates will be reported as proportional odds ratios for the intervention group compared with the control group using logistic regression. For nominal categorial (i.e. count) outcomes, treatment effects will be reported as rate ratios for the intervention group compared with the control group.Efforts will be made to minimise missing data. In case of encountering expected missing data, these will be documented and the reasons for missingness will be explored to enable the researchers to determine the proper imputation mechanism to estimate the missing values.

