**Methods::**

This randomised controlled trial will be conducted at ambulatory dialysis centres, with an internal pilot to assess the feasibility of recruitment, intervention implementation, and safety measures. Patients will be randomised to usual care or an intervention group where a clinical pharmacist, in collaboration with a multidisciplinary healthcare team, will deliver a structured deprescribing intervention, including periodic monitoring over six months. Outcomes will be measured at baseline, three, and six months. The primary outcome is the proportion of patients with at least one potentially inappropriate medication (PIM). Secondary outcomes include pill burden, treatment burden, hospitalisations, emergency department visits, quality of life, and adherence. A cost–benefit analysis will also be performed. A total of 250 patients provides 90% power to detect a 50% reduction in PIM prevalence (α = 0.05). The statistical analysis will be based on the intention-to-treat principle, using mixed-effects models to account for repeated measures.

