#### Primary outcome

***Potentially inappropriate medications (PIMs):*** This is represented as the number of events and non-events in each study group. It will also be reported as the percentage of participants with PIMs. PIMs are defined as drugs for which use should be avoided due to high risk of adverse reactions and/or insufficient evidence of benefit when safer and equally or more effective alternatives are available for this population (Fick et al., 2003). This will be determined through medical records using the MAI tool (Hanlon & Schmader, 2013). This implicit tool helps clinicians in making a comprehensive assessment of medication appropriateness. It contains 10 items to assess the appropriateness based on indication, efficacy, correct dosage, correct directions, practicality of the directions, interactions, duration of therapy, and costs. The medication is considered a PIM if the MAI score is ≥1. The MAI tool was deemed appropriate to identify PIMs among the target population as it provides a comprehensive overview of the prescribed medications. It has previously been used to identify PIMs among CKD patients (Wubshet H Tesfaye et al., 2019). In our assessment, the costs are not considered, given that the healthcare provider in Qatar (HMC) governs the decisions regarding the purchase of medication brands. Consequently, it was impractical for the research team to compare all medication alternatives (as the item of the cost mentioned in the MAI tool).

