### Data management and analysis plan

#### Sample size

Assuming normally distributed outcomes, comparing post-randomisation main outcomes between two groups, the number of subjects per group for a two-sided significance level (α) of 5% and power (1 – β) of 90% is 106. Considering the proportion of PIM (primary outcome) use among CKD patients is 40%, based on previously published studies (Tesfaye et al., 2017). Assuming a target decrease of 50% in the proportion of PIMs in the intervention group compared to the control group (Kua et al., 2019), a total of 212 participants (106 from each group) is needed. To account for a 10% dropout rate, a total of 250 participants will be needed, with 125 participants per group (Naing et al., 2022). While the initial calculation assumed a dropout rate of up to 50%, findings from the pilot study demonstrated that the actual dropout rate did not exceed 10%, supporting the feasibility of the adjusted sample size.

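### The yes/no primary outcome is assigned to Poisson regression with no robust variance stated; with model-based variance the test is too conservative and power is about 81–87%, not 90%, at the planned evaluable size

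*Protocol article*

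**What the plan says.** The outcome is binary in three places in the protocol article.

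- Abstract, Methods: "The primary outcome is the proportion of patients with at least one potentially inappropriate medication (PIM".
- Primary outcome: "This is represented as the number of events and non-events in each study group", also to be given as a percentage of participants.
- Sample size: a control proportion of 40%, and "Assuming a target decrease of 50% in the proportion of PIMs in the intervention group compared to the control group", which means 40% versus 20%. On that basis "the number of subjects per group for a two-sided significance level (α) of 5% and power (1 – β) of 90% is 106", raised to 250 in total: "To account for a 10% dropout rate, a total of 250 participants will be needed, with 125 participants per group".

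The abstract repeats the power claim: "A total of 250 patients provides 90% power to detect a 50% reduction in PIM prevalence".

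Under Detailed analyses approach the method is: "Analysis of PIMs (primary outcome) between groups at 6 months will be performed using Poisson regression with adjustment of baseline values", together with age, comorbidities and dialysis group. No variance estimator is named. The effect measures in that section are mean differences for continuous outcomes, proportional odds ratios for ordinal outcomes, and rate ratios for nominal categorical outcomes, which it equates with counts. Binary outcomes have no entry, and neither a risk ratio nor a risk difference is mentioned.

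The same section, and the abstract, also place the primary outcome under mixed-effects models for the 3- and 6-month data.

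**The concern.** A Poisson model assumes that the variance equals the mean. For a yes/no outcome with probability p the variance is p(1−p), which is smaller. The point estimate, a risk ratio, is not the problem. The model-based standard error is too large, and more so the commoner the outcome and the better the covariates predict it. The sample size, by contrast, rests on the correct binomial variance.

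If the model is run with its model-based variance, the primary confidence interval is too wide and the p-value too large. Much of the precision that baseline adjustment should bring is lost, and a true halving of PIM prevalence is missed more often than the stated 10% of the time. Treating categorical outcomes as counts with rate ratios makes that route more likely, because nothing in the text signals that a binary outcome is being modelled.

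**Working it through.** **Inputs from the Sample size section.** Control 0.40; intervention 0.20; two-sided α 0.05; power 90%; 106 per group; 125 per group recruited; 10% dropout. Evaluable: 125 × 0.90 = 112.5, so about 112 per arm.

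**1. The plan's own figure.** Two proportions, unpooled binomial variance:

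n = (1.960 + 1.282)² × (0.4×0.6 + 0.2×0.8) / 0.2² = 105.07, so 106 per group. This matches exactly, so the sample size does rest on p(1−p).

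**2. Standard error of the log risk ratio, unadjusted.**

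- Poisson, model-based: √[(1/0.4 + 1/0.2)/n] = √(7.5/n)
- Correct for a binary outcome: √[(0.6/0.4 + 0.8/0.2)/n] = √(5.5/n)
- Ratio: √(7.5/5.5) = 1.17

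At 106 per arm the two are 0.266 and 0.228. The 95% interval around a risk ratio of 0.5 is 0.30–0.84 instead of 0.32–0.78.

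**3. Type I error, 40% in both arms.** The ratio becomes √(5/3) = 1.29, and 2 × [1 − Φ(1.96 × 1.29)] is about 1.1% instead of 5%. Simulation gave 1.5% unadjusted and 0.2% with an assumed baseline covariate. With robust variance it gave 4–5%.

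**4. Power, unadjusted.** The test uses the Poisson standard error (SE_P), but the estimate varies with the binomial one (SE_B), so power = Φ[(ln 2 − 1.96·SE_P)/SE_B]. Simulation is the better guide, because the normal approximation runs about 2–3 points low here.

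| Per arm | Model-based, formula | Model-based, simulated | Robust, simulated |
|---|---|---|---|
| 106 | 77.5% | 80% | 89% |
| 112 (formula at 112.5) | 80.1% | 83% | 91% |
| 125 | 84.5% | 87% | 93% |

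**5. Power with baseline adjustment.** The documents give no baseline–outcome association, so three are assumed. In each, 40% have a PIM at baseline, the month-6 control risks average 40%, and the intervention halves every risk.

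| Assumed control risk, PIM at baseline / none | SE ratio | Model-based power, 112 | Model-based power, 125 | Robust power, 112 |
|---|---|---|---|---|
| 50% / 33% | about 1.18 | 82–86% | about 88% | about 91% |
| 70% / 20% | about 1.26 | 84% | about 90% | 94% |
| 85% / 10% | about 1.41 | 87–88% | 90–91% | 98% |

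The spread within a cell is between simulation runs. A stronger baseline association raises power under either variance, but widens the gap between the two.

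**6. If prevalence is higher than planned.** Any drug with an MAI score of 1 or more counts as a PIM, so prevalence might exceed 40% (an assumption). The ratio would be 1.29 at 60% versus 30% and 1.46 at 80% versus 40%. Power for a halving would be less of a worry there, but the reported interval would be further from the truth.

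**The case against.** The strongest reply is that the article never says the variance is model-based. It is a condensed account, the analysis plan is not shown, and Poisson regression with robust variance is a recognised way to estimate a risk ratio for a binary outcome. A reader might infer that plain Poisson regression has been chosen and that the primary interval will be wrong. The text does not support that as fact, so every figure here is conditional on the model-based variance. What remains is that the section is detailed about models, covariates and effect measures, yet has no binary category and equates categorical outcomes with counts. That is a method poorly matched to the stated outcome, and more than an omitted detail.

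Other parts of the reply also stand:

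- The error is conservative. It does not inflate false positives.
- The sample size is sound, and powering on two proportions before an adjusted analysis is ordinary practice.
- Not all of the gap from 90% comes from the Poisson variance. On the log risk ratio scale the correct standard error itself gives 86% by formula, and 89% simulated, at 106 per arm.
- A reader might quote an interval some 40% too wide, or robust power of 98–99%. Those figures need the strongest of the three assumed baseline associations and should not stand as the headline.
- If the mixed-effects model is the deciding analysis, this arithmetic does not apply directly. That shows that the primary analysis is not fixed; it does not remove the problem.

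**Conclusion.** The point holds in conditional form. A binary primary outcome, sized with binomial variance, is assigned to Poisson regression with no robust variance stated. Under the model-based variance:

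- the standard error is about 1.17 times too large unadjusted, and about 1.18 to 1.41 times with baseline adjustment;
- type I error is about 1% or less;
- power is about 81–87% at about 112 evaluable per arm (single runs under the strongest assumed association reach 88%), and about 87–91% if all 125 per arm are retained.

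Robust variance gives about 91% or more at 112 per arm. These figures rest on 40% versus 20%, 10% dropout and, for the adjusted results, the three assumed associations.

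The documents do not support the stronger readings that the sample size is wrong, that false positives are inflated, or that the stated power is certain to be missed. The change alters the primary interval and p-value and costs almost nothing, so it should be fixed. It does not threaten the validity of the trial.

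**What to change.** In Detailed analyses approach, state that the primary outcome, at least one PIM at 6 months (yes/no), is analysed by Poisson regression with log link and robust (sandwich) variance. Logistic regression with marginal standardisation is an acceptable alternative; it is a different model with a similar target. Keep the planned covariates, and report a risk ratio and a risk difference, each with a 95% confidence interval. Add binary outcomes to the list of outcome types and keep the rate ratio for counts.

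Name a single primary analysis: either this one, or the mixed-effects model with a specification suited to a binary outcome. The other becomes supportive. If the full analysis plan already says this, bring the article into line with it.

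The cost is a sentence or two of text and one option in the planned software: SPSS offers robust covariance in its generalized linear models. No new patients or data are needed. The article describes recruitment as ongoing, so this can be settled before analysis.

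### The primary outcome is assigned to two different models with two covariate lists and several tests at 0.05, and the article does not say which one decides the trial

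*Protocol article*

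**What the plan says.** All places are in the Protocol article.

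- **Endpoint.** The Abstract defines the primary outcome as the proportion of patients with at least one PIM. The Primary outcome section reports it as events and non-events and as a percentage of participants.
- **First model.** Detailed analyses approach compares PIMs between groups at 6 months by Poisson regression, "with adjustment of baseline values, age, comorbidities, and dialysis group".
- **Second model.** The same section continues: "Outcomes with repeated measures at 3 and 6 months, including the primary outcome, will be analyzed using mixed-effects models". To compare the arms, "general linear models will include fixed effects for the treatment group, time point, and the interaction between the treatment group and the time point". The effect is to be reported at 6 months whatever the interaction shows.
- **Abstract.** It describes the analysis as mixed-effects models for repeated measures and does not mention Poisson regression.
- **Tests of the primary outcome.** Multiple testing states: "The analyses will perform multiple tests on the unadjusted and adjusted, and possibly sensitivity analyses of the primary outcome". The only multiplicity rule in that section concerns secondary outcomes.
- **Covariates.** Covariates and subgroups states: "Covariates for adjustment in all analyses will include the randomisation stratification variable, gender, comorbidities, and age". It adds that the primary outcome will be baseline-adjusted.
- **Level.** For all analyses, "statistical significance will be assessed at the two-sided 0.05 level".

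No section names one of these analyses as primary, orders them, or splits the 5%.

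**The concern.** The sample size is built on a single two-sided 5% comparison of two proportions, but the analysis sections never identify that comparison. One outcome is given two models, one of them of a form meant for continuous data. It is to be tested both with and without adjustment, although adjustment is said to apply to all analyses. The two covariate lists differ by gender.

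Two things are at stake. If the routes disagree, whichever is significant could be presented as the primary result, and nothing in the article would contradict that. Separately, the routes differ in how well they suit a binary outcome: Poisson regression with its usual standard errors is badly conservative there. So the choice of route can change the verdict in either direction. Providers and patients are not blinded and recruitment is under way, so a choice made after results are seen would be hard to defend.

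**Working it through.** **Inputs from the article.** Control proportion 40%; 50% relative reduction, so 40% versus 20%; "two-sided significance level (α) of 5% and power (1 – β) of 90% is 106" per group; 212 in total, 250 after allowance for dropout. Sample size section.

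**Step 1: reproduce the plan's figure.** Two proportions, unpooled variance:

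n = (1.960 + 1.282)² × (0.4×0.6 + 0.2×0.8) / 0.2² = 105.07, rounded up to 106 per group.

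This matches. The design rests on one test at two-sided 5%.

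**Step 2: false-positive rate if any significant route may carry the claim.** If the tests were independent, the limit would be 1 − 0.95² = 9.75% for two, 14.3% for three and 18.5% for four. They use the same patients and are strongly correlated, so the rate was simulated under no effect, with 40% prevalence and 4,000 trials per setting (Monte Carlo error about 0.4 to 0.5 points). The strength of baseline prognosis is not in the article and is varied as an assumption.

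Setting A: 125 per arm, complete binary data at 0, 3 and 6 months, adjustment for baseline PIM only. The linear 6-month contrast is fitted by least squares as a stand-in for the mixed model.

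| At least one p < 0.05 | Latent correlation 0.3 | 0.6 | 0.8 |
|---|---|---|---|
| Unadjusted, or adjusted Poisson (robust) | 5.9% | 6.5% | 7.9% |
| Adjusted Poisson (robust), or linear at 6 months | 5.2% | 4.6% | 5.5% |
| All three | 5.9% | 6.5% | 8.1% |

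Setting B: 112 per arm, unadjusted or adjusted, indexed by the phi correlation between baseline and 6-month PIM status: 5.1% at phi 0, 6.3% at 0.25, 6.6% at 0.50 and 8.5% at 0.75. The last corresponds to 6-month PIM in 85% of those with and 10% of those without baseline PIM: 0.4×0.85 + 0.6×0.10 = 0.40, and phi = (0.34 − 0.16)/0.24 = 0.75. A separate run at that same split gave 8.8%.

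The inflation therefore comes from unadjusted versus adjusted testing. Poisson versus linear at 6 months contributes almost none.

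**Step 3: Poisson regression with model-based errors.** For a 0/1 outcome with proportion p, the Poisson model takes the variance as p, whereas it is p(1 − p). With p = 0.4 in both arms, the true standard error of the log ratio is √0.6 = 0.775 of the model's. A nominal 1.96 then acts as 1.96/0.775 = 2.53, a true two-sided level of about 1.1% (unadjusted, large-sample). In simulation the adjusted version rejected a true null in 0.3% to 1.0% of trials under Setting A. Unadjusted-or-adjusted, both with model-based errors, rejected in 1.1% to 1.6%.

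**Step 4: what that costs in power.** At 106 per group, expected events are 42.4 and 21.2.

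- Model-based SE of the log ratio: √(1/42.4 + 1/21.2) = 0.266.
- True SE: √(0.6/42.4 + 0.8/21.2) = 0.228.
- Power with the true (robust) SE: Φ(0.693/0.228 − 1.96) ≈ 86%.
- Power with the model-based SE: Φ((0.693 − 1.96×0.266)/0.228) ≈ 77%.

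Intervals are about 17% too wide at the design effect (0.266/0.228), and about 29% too wide when both arms are at 40% (1/0.775). The power figures are unadjusted log-scale approximations.

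**The case against.** The strongest reply is that the article fixes more than it first seems to. The mixed-model effect is reported at 6 months, so both models address the same contrast. Baseline adjustment is promised for the primary outcome, which answers any suggestion that the mixed model goes without it. Adjustment is the rule for all analyses, so an unadjusted result can be read as routine companion reporting, and sensitivity analyses are by name not confirmatory. The general linear wording covers all repeated outcomes and may be loose; mean differences are assigned only to continuous outcomes, so it is nowhere stated that PIMs would be reported that way. The gender mismatch is small. Ranking analyses is often left to a statistical analysis plan.

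Most of this stands, and it limits the point. It does not remove it. The article does not merely omit a ranking: it assigns one outcome by name to two models, its abstract names only one of them, and it announces multiple tests of that outcome. A later plan would have to override one of these statements.

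A reader might infer that the 5% level is certainly exceeded, or exceeded by as much as the 14% to 18% of independent tests. The documents do not support that. Inflation requires that the best result be picked and that robust variance, which the article does not mention, be used. With model-based Poisson errors the error goes the other way.

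**Conclusion.** The conflict is real and is stated in the text. The 6-month time point and baseline adjustment are settled; the model, the covariate list and the status of the unadjusted test are not. If any significant route may carry the claim, the false-positive rate for unadjusted or adjusted tests with robust variance is about 5% to 9%, rising with the assumed prognostic strength of baseline PIM status. Model-based Poisson errors on the binary outcome give a true level of about 1% and cost roughly 9 points of power at 106 per group (86% to 77% in the approximation above).

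The figures rest on complete data, 40% prevalence, adjustment for baseline PIM only, and an assumed correlation between visits. This should be fixed. It does not invalidate the design: the 106 per group stands once one test is named.

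**What to change.** Before unblinded data are seen, revise Covariates and subgroups, Multiple testing and Detailed analyses approach, and align the Abstract:

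1. Name one analysis of at least one PIM (yes/no) at 6 months as primary. Either Poisson regression with robust variance, or a binary-outcome GEE or generalized linear mixed model with the 6-month contrast, is defensible. State its effect measure.
2. Use one covariate list: dialysis stratum, gender, comorbidities and age, as in Covariates and subgroups, plus baseline PIM status.
3. Remove the general linear description for this outcome.
4. State that the conclusion rests on this test alone at two-sided 0.05. Label the unadjusted, sensitivity and other-model analyses as supportive.

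The cost is wording. The sample size is unchanged, no new data are needed, and the supportive analyses can still be run and reported.
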